### Outcomes {12}

The investigation presented herein offers a comprehensive examination of the gut microbiota, cytokines, and proteins involved in neuroplasticity and aging control. This study will obtain demographic variables, including year and date of birth, age, sex, educational background, past medical history, present illness history, current medication and supplements, height, and body weight. Executive function will be assessed using the Stroop, flanker, and N-back tasks (1-back and 2-back). Memory function will be assessed using a source-memory task. Questionnaires about psychological characteristics will assess grit (a Japanese translation of the 8-item Short Grit Scale), resilience (the 6-item Brief Resilience Scale-Japanese version), and mindset (the Japanese version of the Self-Theories of Intelligence Scale). Additionally, the Japanese versions of the 6-item Kessler Psychological Distress for Depression and the 10-item Japanese version of the Perceived Stress Scale for measuring perceived stress will be used. This study will assess physical activity using Global Physical Activity, Mood, Constipation, Sleep state, and QOL. The detailed descriptions are provided below. Furthermore, this study will assess physical function by measuring hand grip strength, conducting a 5-m walk test, and evaluating single-leg support.

The primary objective of this study is to elucidate the effects of exercise-induced cytokines and proteins involved in the control of aging on cognitive function. To date, no studies have thoroughly explored these associations. This study aims to provide pioneering insights into the relationship between exercise and brain function, thereby establishing a foundation for future research. As a secondary outcome, an exploratory investigation will examine the relationship between the gut microbiota and protein analysis from blood samples. This approach will enable a deeper understanding of the biological processes involved and may lead to targeted interventions that promote cognitive health.

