## Assignment of interventions: allocation

### Sequence generation {16a} and Allocation concealment mechanism {16b}

This study will be conducted as an open-label, randomized controlled trial. Thus, the participants will be randomly assigned to the circuit training or wait-list groups in a 1:1 ratio. Simple randomization will be performed using Research Randomizer (www.randomizer.org), a computer-based random number generator. This web-based service will be used to generate the random sequence for participant allocation to either the circuit training or control group. To ensure allocation concealment, the random allocation sequence will be generated only after each participant is deemed eligible and formally enrolled based on the inclusion and exclusion criteria. Participants will be informed of their group assignments to complete the pre-examination.

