### Statistical methods

#### Statistical methods for primary and secondary outcomes {20a}

The statistical analyses will be performed using Python, R, Stata, and Mplus. The significance threshold for all statistical analyses will be set at *p* < 0.05. When the statistical analysis does not find statistical significance for our outcome based on our hypothesis, a 95% confidence interval will be used to estimate the effects of exercise. For cognitive performance, aging control factors, specific gut bacteria, and linear mixed model (LMM) analyses will be performed, including age and sex as covariates. The primary outcomes will be assessed as follows:

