◦ We will use structural equation modeling (SEM) or mediation models to test whether changes in specific proteins or gut microbiota mediate the relationship between the exercise intervention and improvements in cognitive function.◦ For instance, if SCFA-producing bacteria increase in the exercise group, we will examine whether these changes lead to alterations in SIRT/mTOR signaling, which subsequently improve cognitive performance.Psychological and physical assessments◦ Grit, Resilience, Mindset, Depression, Stress, Quality of Life, and physical function measures will be incorporated into SEM analysis to examine how these psychological factors may mediate exercise-induced cognitive improvements.

In our primary analysis, an LMM is conducted to examine cognitive performance, gut microbiota, and aging control factors. As a secondary analysis, we will perform a linear model analysis using the Elastic Net approach for omics analysis and SEM to further explore the relationships among exercise, protein expression, psychological characteristics, mental health, and Quality of Life (QOL). Specifically, we will employ SEM to examine both the direct effect of exercise on cognitive function and explore potential indirect (mediating) effects through grit and resilience measures. We will randomly assign participants into exercise vs. control groups in a 1:1 ratio, ensuring that baseline variability in gut microbiota, cytokines, and protein levels is minimized across groups. Specifically,Randomization will be used to minimize systematic bias in baseline cognitive function, microbial and proteomic profiles.Baseline adjustments:◦ We will apply a linear mixed model with random intercept for adjustment of baseline conditions. Since this study will employ a randomized study design, baseline differences may be attributed to chance. For example, randomized intervention studies used a linear mixed model for assessing the effects of exercise on cognitive function [70–72] without adjustment for baseline conditions

By combining randomization with rigorous statistical adjustment, we can isolate the effects of the exercise intervention on outcome changes and reduce confounding from individual differences in biomarker levels.

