From a different perspective, Nouchi and Nouchi [75] discovered that circuit training exercises increase vigor-activity mood scores in middle-aged and older populations. Thus, based on a previously established association, long-term combination exercise may alter psychological characteristics and improve mental health [76–78]. Furthermore, it is expected that the gut microbiota and factors controlling aging are involved in psychological characteristics and mental health. This study plans to use SEM analysis to unravel the complex relationships between exercise, gut microbiota, aging control factors, cytokines, and proteins involved in neuroplasticity and aging control, psychological characteristics, mental health, and QOL. Elucidating these causal relationships can help reveal the potential effects of circuit training exercises on aging populations.

Nonetheless, a notable limitation of this study is the lack of dietary intake monitoring. While this approach reflects a real-world setting where participants maintain their usual dietary habits during the exercise intervention, it may limit our understanding of the relationship between exercise and changes in gut microbiota. Future research should consider incorporating dietary controls to better understand how dietary patterns might influence the gut microbiota response to exercise.

Our findings advance the current understanding of exercise-induced cognitive enhancement in several important ways. First, we integrate exercise science, gut microbiota analysis, and aging research to demonstrate how shorter-duration circuit training (30 min) can effectively promote cognitive health through multiple physiological pathways. Second, our exploratory analyses of gut microbiota and protein expression provide novel insights into the potential mechanisms through which circuit training may influence cognitive function, opening new avenues for future research in exercise neuroscience. Finally, by delineating the relationship between exercise adherence, grit, and resilience using SEM, we offer practical implications for developing sustainable exercise interventions that can be readily adopted in daily life. These insights could inform future intervention studies aimed at preventing cognitive decline in aging populations while ensuring practical feasibility in real-world settings.

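### Randomising exercise does not identify the biomarker-to-cognition path, so the planned mediation models cannot support the causal reading the article gives them

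*Protocol article*

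**What the plan says.** Participants are "randomly assigned to the circuit training or wait-list groups in a 1:1 ratio"; nothing else is randomised. Under Statistical methods {20a}, in the item on mediation and path analysis, structural equation modelling (SEM) or mediation models will be used "to test whether changes in specific proteins or gut microbiota mediate the relationship between the exercise intervention and improvements in cognitive function". The example given is a serial chain from short-chain-fatty-acid-producing bacteria through SIRT/mTOR to cognitive performance.

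Outcomes {12} says that randomised assignment combined with multi-level statistical methods allows possible mediating mechanisms to be elucidated. The Discussion says of the SEM: "Elucidating these causal relationships can help reveal the potential effects of circuit training exercises on aging populations".

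On adjustment, section {20a} describes the linear mixed models as "including age and sex as covariates", and adds baseline values for the gut and protein models. It also states "We will apply a linear mixed model with random intercept for adjustment of baseline conditions". No covariate is stated for the SEM. The Discussion concedes that "a notable limitation of this study is the lack of dietary intake monitoring", but ties this only to the relationship between exercise and gut microbiota.

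On status, section {20a} places the mediation analysis among the secondary (exploratory) outcomes. Objectives {7}, however, makes the chain from exercise through microbiota, proteins and cytokines to cognition the central hypothesis.

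**The concern.** A mediation claim needs two links: exercise changes the biomarker, and the biomarker changes cognition. Randomisation secures the first link and the total effect of exercise on cognition. It does not secure the second. Within each arm, participants whose biomarker changed more may differ in diet, medication, sleep or activity outside the programme, and these may also affect test performance.

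An indirect effect is the product of the two links. If exercise moves the biomarker, confounding of the second link carries into the product. The trial could then report a biological mechanism where the biomarker has no effect on cognition, or miss one that exists. Crediting randomisation with elucidating mechanisms, and calling the SEM results causal, gives the second link a protection it does not have. Some candidate causes are recorded and a later plan could use them. Diet is not recorded, so this gap cannot be closed at the analysis stage.

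**Working it through.** **The plan's own figure.** The article gives no number for the mediation analysis, only a total of 46 before dropout (f = 0.25, power 0.9, alpha 0.05). For a two-group, two-time interaction with within-person correlation 0.5 (assumed; none is stated), the noncentrality is f² × N × 2/(1 − 0.5) = 0.0625 × 46 × 4 = 11.5. This gives power 0.912 at 46 and 0.8997 at 44, so 46 is reproduced. Then 46/0.9 = 51.1, which the article states as approximately 51. I use 46 as the number analysed.

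**Set-up for the mediation check.** The biomarker change has within-arm SD 1 and is shifted by a SD under exercise. The cognition change does not depend on the biomarker. One shared cause, varying over the 16 weeks, correlates c with each change within arm. Mediation is declared when both paths have p < 0.05. The documents give neither a nor c; both are assumptions and are varied.

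**Formulae.** With equal correlations and no true effect, the within-arm correlation between the two changes is c × c = c². The biomarker coefficient in the cognition model therefore centres on c² instead of 0, and the spurious indirect effect is about a × c². The exercise-to-biomarker path has noncentrality a/(2/√46):
- a = 0.8: 0.8/0.295 = 2.71, power 0.76
- a = 0.5: 0.5/0.295 = 1.70, power 0.38

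**Results** (simulation, 40,000 trials per cell):

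| c | c² | Biomarker-cognition path significant | Spurious indirect effect, a = 0.8 | False mediation, a = 0.8 | False mediation, a = 0.5 |
|---|---|---|---|---|---|
| 0 | 0 | 5% | 0 | 4% | 2% |
| 0.3 | 0.09 | 9% | 0.07 SD | 7% | 4% |
| 0.5 | 0.25 | 39% | 0.20 SD | 29% | 14% |
| 0.6 | 0.36 | 70% | 0.29 SD | 52% | 26% |

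Multiplying the two path probabilities agrees closely: at a = 0.8 and c = 0.5, 0.76 × 0.39 = 0.30; at a = 0.5, 0.38 × 0.39 = 0.15. Other runs with 3,000 to 4,000 trials per cell gave 28% to 30% and 13% to 14% for these two cells. With the shared cause in the model, the false rate at a = 0.8 is 4% to 5% throughout.

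**Limits of the bias.**
- If exercise does not move the biomarker (a = 0), the false rate stays at or below about 5%, even when the cause explains half of the residual variance in both changes.
- A stable additive cause largely cancels in change scores, leaving a false rate of about 5%.
- A cause acting in opposite directions hides mediation. With a true biomarker coefficient of 0.3, a = 0.8 and a cause explaining 30% of the residual variance, detection falls from 36% to 4%.

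**What adjustment is in place.** Age, sex and baseline values are stated for the mixed models. Eligibility {10} admits women only, so sex is constant. Stress, depression, quality of life and physical function enter the SEM as possible mediators, not as confounders of the protein or gut paths.

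**The case against.** The strongest reply is that this is a condensed article and that the covariate set for an SEM is commonly left to the analysis plan. That stands: silence on covariates does not show that the model will be unadjusted, and the omission alone would be no finding. Medication is also to be reported so that its effect on cognition can be considered, and a physical-activity analysis is planned. The reply does not reach two things the article itself fixes: the causal wording, and the absence of diet data.

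Four stronger readings are tempting but unsupported.
- A reader might infer that any shared cause will appear as mediation. It will not, for the reasons listed under the limits of the bias.
- A reader might infer that age and sex are the only covariates in the plan. Baseline values are also stated for the gut and protein mixed models.
- A reader might take the promise to "reduce confounding from individual differences in biomarker levels" as a claim that the mediator path is unconfounded. That sentence closes the text on randomisation and baseline adjustment and concerns the effect of the intervention on outcome changes. Those are arm contrasts, which randomisation does support.
- A reader might infer from the sentence "The primary objective of this study is to elucidate the effects of exercise-induced cytokines and proteins involved in the control of aging on cognitive function" that the SEM supplies the trial's primary result. The primary outcome is cognitive function, compared between arms by mixed model, and the SEM is labelled secondary and exploratory.

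The exploratory label lowers the weight of the point. It does not reconcile that label with a central hypothesis of mediation and results described as causal.

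**Conclusion.** The concern holds in limited form. The randomised comparisons of cognition and of biomarkers are sound on this point. The causal reading of the mediation models is not supported, because the biomarker-to-cognition path is observational and at least one plausible time-varying shared cause is unmeasured.

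The size depends entirely on assumed values: from almost no inflation (7% against 4%) at correlation 0.3 to about half of trials at 0.6, with a 0.8 SD shift, and roughly half those rates with a 0.5 SD shift. These figures show what could happen; they do not estimate what will. The point should be corrected because it changes what the trial may conclude about mechanism, but it does not threaten the trial's main comparison.

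**What to change.** In the mediation item of section {20a}, specify the cognition equation as week-16 cognition on arm and week-16 mediator, adjusted for baseline cognition, baseline mediator, age and education, all of which are collected. In sensitivity checks, add further covariates (physical activity, sleep quality, medication and supplements) at their pre-randomisation values only. Week-16 values can be changed by exercise, and the activity questionnaire may count the training itself.

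Report the residual mediator-outcome correlation at which the indirect effect becomes zero. Baseline covariates cannot remove causes that change during the 16 weeks, and diet was not recorded, so this is the check that bears on them.

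Reword Outcomes {12}, section {20a} and the Discussion so that only arm contrasts are called causal and the mediator-cognition path is an exploratory association. Extend the diet caveat to that path.

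The cost is a little more analysis on data already collected, and weaker claims about mechanism.

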### Objectives {7}

Although accumulating evidence has demonstrated the positive impact of aerobic and resistance training by clarifying the underlying mechanisms, the positive effects of circuit training on the brain and cognitive performance remain unclear. Thus, this study aims to clarify the effects of long-term circuit training on executive and memory functions from a comprehensive perspective in terms of the gut microbiota, cytokines, and proteins involved in neuroplasticity and aging control. We hypothesize that long-term circuit training improves executive and memory functions. Furthermore, this relationship is likely mediated by the gut microbiota and aging control factors through proteomic analysis. Our central hypothesis is that exercise intervention will modulate gut microbiota composition and metabolite (e.g., increasing short-chain fatty acid [SCFA]-producing bacteria), leading to changes in key aging-related proteins (e.g., SIRT, mTOR) and cytokines (both pro- and anti-inflammatory), which in turn will positively affect cognitive function and neuroplasticity. We hypothesize the following mechanism:

Exercise → shifts in gut microbiota diversity/composition → increased SCFA levels → enhanced neuroplasticity and cognitive function;Exercise → altered cytokine profiles → modulation of SIRT/mTOR pathways → enhanced neuroplasticity and cognitive function.

Additionally, we hypothesize that the circuit training group will show superior cognitive outcomes compared with the control group. In addition, we will explore the underlying mechanisms through gut microbiota and proteomic analyses, as well as psychometric assessments of psychological factors.

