By combining randomized assignment with multi-level statistical methods, we can:Measure how the exercise intervention alters gut microbiota/metabolite, inflammatory/anti-inflammatory cytokines, and aging-related proteins;Identify the biomarkers or pathways most strongly associated with improvements in cognitive outcomes; andElucidate possible mediating mechanisms (e.g., exercise → gut microbiota → SCFA → cognition, exercise → SIRT/mTOR → cognition).

The primary outcome of this study is cognitive function, which will be assessed by comparing changes from baseline to 16 weeks after the intervention. We will evaluate four key cognitive domains using standardized tasks. Executive function and attention will be measured using a paper-and-pencil version of the Stroop task, analyzing changes in both reaction time (milliseconds) and error rates. Selective attention and response inhibition will be assessed using a computerized Flanker task, measuring changes in accuracy (percentage of correct responses) and reaction time. Working memory capacity and updating will be evaluated using an n-back task (with *n* = 1 and *n* = 2 conditions), examining changes in accuracy and reaction time. Finally, hippocampal-dependent memory function will be assessed through a source memory task, measuring changes in accuracy of responses. All these measurements will compare performance between baseline (week 0) and the end of the intervention period (week 16). In terms of compliance criteria and statistical analysis of non-compliance, participants must attend at least two sessions per week. Based on previous research [44] demonstrating cognitive improvements with ≥ 70% attendance, we will establish a 70% compliance threshold. For the main analysis, we will include participants who completed both pre- and post-intervention assessments, with missing data handled using the multiple imputation method and a machine learning approach, such as random forests. Furthermore, if notable variation in attendance occurs, we will conduct stratified analyses using the 70% threshold to explore potential dose–response relationships.

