### Gut microbiota

Participants will be instructed to collect fecal samples at home using the Metabolokeeper® preservation solution (TechnoSuruga Laboratory, Shizuoka, Japan) before the pretest and after completing the intervention period. Each participant will be provided with a collection kit containing a sterile collection tube prefilled with 5 mL of Metabolokeeper. All fecal samples will be sent to Technosuruga Laboratory Co., Ltd. for analysis of gut microbiota composition. The sample using a microbiome analysis reveals α and β diversities, as well as levels of SCFAs. The analysis will involve extracting DNA from fecal samples using an amplicon sequencing method. The DNA will then be amplified by polymerase chain reaction (PCR). Subsequently, the V3-V4 region of the 16S ribosomal RNA (rRNA) region will be targeted for sequence analysis using the Illumina MiSeq system, and the data is processed using QIIME2 software [66]. The taxonomic assignment of representative sequences will be performed using the Greengenes database [66]. Additionally, a physicochemical analysis of the fecal samples will be performed to detect SCFAs based on the metabolism of dietary fibers and carbohydrates by the gut microbiota.

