### Factors of aging control

The proteome analysis method to be employed in this study will allow for the quantitative measurement of proteins. This method utilizes a technology based on aptamers designed to exhibit specific affinity toward target molecular structures, thereby enabling the detection of various protein configurations. Proteomic analysis can measure approximately 1000 different types of proteins. The analysis in this study will primarily reveal the cytokines related to the immune system. Furthermore, we will focus on identifying key proteins relevant to our research, including mTOR and SIRT, which are recognized as factors involved in the control of aging. For this purpose, blood samples from the participants will be analyzed using proteomic analysis.

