### Plans for collection, laboratory evaluation, and storage of biological specimens for genetic or molecular analysis in this trial/future use {33}

Participants will undergo blood sampling before and after the study. Approximately 10 ml of blood sample will be obtained. The collected samples will be analyzed for complete blood count, including red blood cell (RBC) count, hemoglobin (Hb), hematocrit (Hct), mean corpuscular volume (MCV), mean corpuscular hemoglobin (MCH), mean corpuscular hemoglobin concentration (MCHC), platelet count, and white blood cell count (WBC), as well as blood metabolites. These blood samples will also be used for omics analysis.

The blood used for proteome analysis will be processed using a centrifuge to separate serum and plasma. The serum will be discarded, and the plasma will be stored at − 80 °C in a secure, temperature-controlled environment at Tohoku University for a period of 5 years following the completion of the study. After 5 years, all stored plasma specimens will be systematically destroyed in accordance with institutional guidelines and relevant regulations to ensure the protection of participant confidentiality and data integrity. Fecal samples will be sent to TechnoSuruga Laboratory Co., Ltd. for comprehensive gut microbiome analysis. After the completion of the analysis, all fecal specimens will be disposed of properly.

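### The mediation analysis is presented as testing an ordered causal chain, but with one pre and one post value per variable it can only show concurrent associations of changes

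*Protocol article*

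**What the plan says.** Objectives {7} state a chain as the central hypothesis: exercise shifts the gut microbiota and its metabolites, this changes aging-related proteins and cytokines, "which in turn will positively affect cognitive function and neuroplasticity". Outcomes {12} says that randomised assignment together with multi-level methods makes it possible to elucidate possible mediating mechanisms, and gives two example chains ending in cognition.

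Statistical methods {20a}, under Primary outcomes, places a mediation/path analysis among the secondary (exploratory) outcomes. Either SEM or a mediation model will be fitted, and the stated purpose is "to test whether changes in specific proteins or gut microbiota mediate the relationship between the exercise intervention and improvements in cognitive function". The worked example supposes a rise in SCFA-producing bacteria; then "we will examine whether these changes lead to alterations in SIRT/mTOR signaling, which subsequently improve cognitive performance".

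On timing, Outcomes {12} places the cognitive tests at weeks 0 and 16. Stool is collected "before the pretest and after completing the intervention period". For blood, "Participants will undergo blood sampling before and after the study". Section {18a} gives baseline and 16 weeks for all questionnaires.

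On what is measured, Factors of aging control says: "The proteome analysis method to be employed in this study will allow for the quantitative measurement of proteins". The Discussion, having listed what the SEM will relate, says: "Elucidating these causal relationships can help reveal the potential effects of circuit training exercises on aging populations". The limitation it discusses is that diet is not monitored.

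**The concern.** A claim that one change leads to a second, which subsequently improves a third, is a claim about order and cause. The schedule in the text provides neither a mid-intervention measurement nor a manipulation of any mediator. A significant indirect effect could then be reported as the mechanism by which exercise acts, although a reversed order or a shared cause would explain the same data.

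The matter is not peripheral. Outcomes {12} describes the primary objective as elucidating how exercise-induced cytokines and aging-control proteins affect cognition. That is the mediator-to-outcome link, the part that randomisation does not protect.

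**Working it through.** **1. What is observed, and when**

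| Link in the chain | Occasions in the text | Section |
|---|---|---|
| Exercise | randomised at the start | {16a}, {16c} |
| Microbiota, SCFA | one before, one after | Gut microbiota |
| SIRT/mTOR, cytokines | one before, one after | {33} |
| Psychological scales | baseline, 16 weeks | {18a} |
| Cognition | weeks 0 and 16 | Outcomes {12} |

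Each variable yields one change score, and all the scores span the same period. Exercise precedes them all; nothing shows which of the others came first.

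**2. What randomisation identifies**

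Let X be exercise, M a mediator change and Y the cognitive change:

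- M = a·X + e_M
- Y = c′·X + b·M + e_Y
- indirect effect = a·b; total effect c = c′ + a·b

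Randomising X identifies a and c. Reading b as causal further requires that M acts on Y and not the reverse, and that e_M and e_Y are uncorrelated. Randomisation secures neither. If the true b is 0 but the residuals (unit SD) have correlation r, the fitted b tends to r and the apparent indirect effect to a·r.

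**3. Sample size used in the checks**

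Sample size {14} gives f = 0.25, α = 0.05, power 0.90 and N = 46. For a group-by-time test with two groups, two measurements and an assumed within-person correlation of 0.5, λ = 0.25² × 46 × 2 / (1 − 0.5) = 11.5 on 1 and 44 df. Power is 0.9125, so 46 reproduces. It was set for the comparison of means, not for mediation; it serves here only as an input.

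**4. Illustration of shared-cause confounding (assumed inputs)**

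Take a = 0.5 SD, c = 0.3 SD and no true mediation.

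| r | a·r | share of c | simulated mean |
|---|---|---|---|
| 0.2 | 0.5 × 0.2 = 0.10 | 0.10/0.3 = 33% | 0.100 |
| 0.3 | 0.5 × 0.3 = 0.15 | 0.15/0.3 = 50% | 0.149 |
| 0.4 | 0.5 × 0.4 = 0.20 | 0.20/0.3 = 67% | 0.202 |

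The simulation had 23 per arm and 2,000 runs. In a rerun with 8,000 runs, both paths were significant in 10%, 20% and 30% of runs respectively.

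**5. Can the planned test tell the structures apart?**

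Simulation with N = 46, 4,000 runs per cell and an assumed mediator-cognition correlation of 0.5 within arm. Exercise acts with effect d on the mediator (true mediation), on cognition (reverse order) or on both (common cause).

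| True structure | M–Y path significant (d = 0.5 / 1.0) | Both paths significant (d = 0.5 / 1.0) |
|---|---|---|
| Mediator causes cognition | 95% / 95% | 36% / 86% |
| Cognition causes mediator | 95% / 95% | 13% / 36% |
| Unmeasured common cause | 94% / 94% | 36% / 86% |

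The common-cause row matches the true-mediation row. The reverse-order row is lower because there exercise reaches the mediator only through cognition, with effect 0.5 × d. At d = 1.0 that effect is 0.5 and the joint test is positive in 35.5% of runs; true mediation with an effect of 0.5 gives 35.8%. The lower rate thus reflects a smaller exercise-to-mediator effect, not an ability to detect direction.

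Model fit does not supply the order either. In one simulated data set, all six orderings of gut, SIRT/mTOR and cognition, with every path included, gave the same log-likelihood (−175.561971).

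**The case against.** **The analysis is labelled exploratory and is often hedged.** This is true. It is listed as secondary (exploratory), several sentences speak of possible or potential mechanisms, and the SIRT/mTOR sentence is an example. This lowers the severity. It does not remove the point, because a label changes the weight of a result, not what the data can identify, and the Objectives and Discussion still use sequential and causal wording.

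**Diet is already disclosed.** This is partly so. The Discussion raises it for the exercise-microbiota relation, not as a possible shared cause of microbiota and cognition, and does not mention temporal order.

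**Equal likelihood proves nothing about timing.** Correct: it is an algebraic property of saturated models with one value per variable, whenever sampled. A model with paths omitted may fit one order better, but only through untested restrictions.

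**A sensitivity analysis belongs in the analysis plan.** Fair, and that plan is not shown. Its absence is not counted as a fault; it is offered as part of the remedy.

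**Stronger readings that a reader might infer.**

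- That stool is sampled after the cognitive outcome. The text says only that it follows the intervention period, and the abstract also places the cognitive tests after the intervention. Table 1 and Fig. 2, where visit-level order would appear, are not available.
- That moving the final samples ahead of the tests would cure the problem. The changes would still cover essentially the same 16 weeks, and a shift within a trial already under way would give early and late participants different sampling times.
- That 33% to 67% is the expected bias. Those figures are a × r divided by c, under assumed values of all three.

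**Conclusion.** The concern holds as a mismatch between claim and design. The text presents the SEM and mediation analysis as a test of an ordered causal chain, but the order among gut, protein and cognitive changes is not observed and the mediator-to-cognition link is not protected by randomisation. Reverse order or an unmeasured common cause would serve as well as mediation to explain a positive result.

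No figure in the documents fixes the size of any bias. The simulations rest on assumed effects and correlations and show only that, at N = 46, a significant mediator-cognition path is about equally likely (94% to 95%) under all three structures. The timing statement rests on the text, which consistently gives two occasions.

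A smaller mismatch goes with it: the mediation example names SIRT/mTOR signalling, whereas Factors of aging control and the primary-outcome list describe protein quantity or expression level.

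The effects of exercise on each mediator and on cognition remain estimable, and the primary LMM comparison of cognition is unaffected. The correction should be made because it governs what may be concluded about the central hypothesis.

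**What to change.** 1. In Objectives {7}, Outcomes {12}, the mediation item of Statistical methods {20a} and the Discussion, state that the SEM estimates concurrent associations of changes that are consistent with mediation but cannot establish order or cause. Remove *causal*, *lead to* and *subsequently* as descriptions of what is tested.
2. List the lack of temporal order as a limitation beside the lack of dietary data, and name diet as one possible common cause of mediator and cognitive changes.
3. Report each indirect effect with a sensitivity analysis over a range of mediator-outcome residual correlation, for example 0 to 0.4.
4. In the mediation item, call the mediator SIRT/mTOR protein level, in line with Factors of aging control and the primary-outcome list.

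The cost is wording changes and one added analysis, with no new samples or visits, so it remains feasible although recruitment began in June 2024. The real price is a weaker mechanistic claim.
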